### Study procedures/interventions

In all patients, capillary glucose will be measured every 60 minutes, starting 30 min prior to surgery. The target range for plasma glucose for all study arms is 6–8 mmol l^−1^. An intravenous bolus of insulin will be administered according to treatment algorithm (Table 4). Capillary glucose will be measured using the Accu-Chek Inform (Roche diagnostics, Indianapolis, IL, USA).

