The day before surgery, the evening dose of long acting insulin will be reduced by 50%.On the day of surgery:○ *If patients are using mealtime and longacting insulin/NPH*: mealtime morning dose will be withheld.○ *If patients are using only long acting insulin/NPH*: the dose of long-acting or NPH insulin will be reduced by 50%○ *If patients are using glucose lowering tablets*: glucose lowering tablets will be withheld on the morning of surgery.Measure glucose every 60 min, start 30 min prior to surgeryAdjust glucose according to treatment algorithm

Subjects in the liraglutide arm (LG) will receive:

On the day before surgery 0.6 mg liraglutide will be administered subcutaneously (s.c.) at 17.00 hr (5 pm). The dose of long acting and mealtime insulin will be reduced by 50% from the start of liraglutide treatment.On the day of surgery own insulin and oral glucose lowering tablets will be withheld.In case of nausea graded higher than minimal, the second gift of liraglutide will be omitted. Otherwise, treatment will be continued with 1.2 mg liraglutide s.c. on the morning of surgery.Measure glucose every 60 min, start 30 min prior to surgeryAdjust glucose according to treatment algorithm

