### Laboratory measurements

HbA1c, potassium and fasting serum glucose will be determined 1 h prior to surgery. Fasting serum glucose and potassium will be determined 1 hour, 4 hours and on day 1 postoperatively. When the patient has an arterial catheter during the surgical procedure, arterial glucose will be measured.

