### Analyses

Statistical analyses will be performed using SPSS version 21.0 (SPSS Inc., Chicago, IL, USA). All data will be analysed according to an intention-to-treat analysis. No interim analysis is planned. Glucose is not normally distributed, thus the between group difference in median glucose at 1 hour, 4 hours and 1 day postoperatively will be tested with the Kruskal-Wallis test and post-hoc testing using the Mann–Whitney *U* test. In case of missing glucose at one hour, the last glucose measured during surgery will be carried forward. Change in glucose will be analysed using repeated measurements ANOVA, with time as fixed effect and baseline glucose, time and the interaction between treatments as covariates. Furthermore a per-protocol analysis will be performed next to the intention-to-treat analysis. Finally, the between group differences of the secondary outcomes will be tested with the ANOVA, Kruskal-Wallis, student *t*, Mann–Whitney *U* and the Chi-square test, where appropriate.

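### The change-in-glucose model adjusts for a glucose value that follows the start of assigned treatment, and its terms are mis-stated

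*Protocol article*

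**What the plan says.** All references are to the Protocol article.

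- **Model (Analyses).** Change in glucose is analysed by repeated-measures ANOVA, "with time as fixed effect and baseline glucose, time and the interaction between treatments as covariates". The term baseline glucose is not defined there or elsewhere.
- **Earliest serum value (Laboratory measurements).** "HbA1c, potassium and fasting serum glucose will be determined 1 h prior to surgery".
- **Earliest capillary value (Study procedures/interventions).** "capillary glucose will be measured every 60 minutes, starting 30 min prior to surgery".
- **Liraglutide arm, evening before.** "On the day before surgery 0.6 mg liraglutide will be administered subcutaneously (s.c.) at 17.00 hr (5 pm"). For insulin, "The dose of long acting and mealtime insulin will be reduced by 50% from the start of liraglutide treatment".
- **Liraglutide arm, day of surgery.** "On the day of surgery own insulin and oral glucose lowering tablets will be withheld". Unless nausea is more than minimal, a second dose follows: "Otherwise, treatment will be continued with 1.2 mg liraglutide s.c. on the morning of surgery".
- **Bolus arm.** The evening long-acting dose is halved. On the day of surgery, patients using only long-acting or NPH insulin still receive some of it: "the dose of long-acting or NPH insulin will be reduced by 50" per cent. Patients who also use mealtime insulin have the morning mealtime dose withheld.
- **GIK arm.** The evening long-acting dose is halved, and insulin and tablets are withheld on the day of surgery.
- **Recruitment visit (Study outline).** The items listed are age, weight, length, history and medication. No glucose value is described.

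**The concern.** A baseline covariate is safe in a randomised comparison because allocation cannot have influenced it. Here the only candidates the article describes are read the morning after assigned treatment began. Liraglutide is given as pre-treatment, so whatever it does to glucose before incision is part of the strategy being tested. The arm-specific insulin rules act before the same readings. Holding that glucose value constant removes one pathway of the assigned strategy from the contrast, and the remainder answers a different question from the one the trial poses. The longitudinal result could then disagree with the unadjusted 1 h comparison for a reason that lies in the model rather than in the treatments.

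Separately, the sentence does not define a model that an analyst could fit without guessing. Time is entered twice, treatment has no main effect, and an interaction between treatments has no meaning for three parallel arms.

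**Working it through.** **1. The plan's own figure.** The Sample size calculation gives SDs of 1.8 and 2.4, a difference of 1 mmol/l, 90% power, 5% significance (two-sided assumed) and 10% drop-out.

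n per arm = (1.8² + 2.4²) × (1.960 + 1.282)² / 1² = 9.00 × 10.507 = 94.57. Dividing by 0.9 gives 105.07.

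The stated 105 per arm reproduces. It relates to the unadjusted comparison and is not touched by this point.

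**2. Order of events for a liraglutide patient.**

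| When | Event |
|---|---|
| Recruitment visit | no glucose described |
| Day before, 17.00 hr | first liraglutide dose; long-acting and mealtime insulin halved from here |
| Morning of surgery | second dose unless nauseated; own insulin and tablets withheld |
| 1 h before surgery | first serum glucose |
| 30 min before surgery | first capillary glucose |

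The first dose and the evening insulin change precede both readings. Whether the second dose also precedes them depends on the hour of surgery, which the article does not fix; the conclusion does not need it. The insulin rules are not the same in all arms, so in insulin users the contrast between GIK and bolus can be affected too.

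**3. What the adjustment does.** Let T be the total effect of the liraglutide strategy on postoperative glucose, d the difference in pre-operative glucose that the strategy itself causes, and b the within-arm slope of post- on pre-operative glucose. Then

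adjusted contrast = T − b × d.

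Neither b nor d is in the article. Both are assumed below, with T = −1.0 mmol/l for illustration.

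| d (mmol/l) | b = 0.3 | b = 0.5 | b = 0.7 |
|---|---|---|---|
| +0.5 | −1.15 | −1.25 | −1.35 |
| 0 | −1.00 | −1.00 | −1.00 |
| −0.25 | −0.925 | −0.875 | −0.825 |
| −0.5 | −0.85 | −0.75 | −0.65 |
| −1.0 | −0.70 | −0.50 | −0.30 |

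Example: −1.0 − 0.5 × (−0.5) = −0.75. A simulation of that case (2,000 runs, 95 per arm) gave −1.01 unadjusted and −0.75 adjusted.

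**4. What the missing main effect can do.** Take a constant effect of −1.0 at 1, 4 and 24 h. If time is linear and treatment enters only through time by arm, least squares returns contrasts of −0.05, −0.20 and −1.17. With an arm main effect added, or with categorical time fully crossed with arm, it returns −1.0 at each time. The harm therefore depends on how the sentence is read, which is why it needs correcting.

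**The case against.** **The timing of baseline is inferred.** The article condenses a fuller protocol, and its list of recorded items is not exhaustive: liver enzymes and creatinine are eligibility criteria, yet their measurement is not described either. An earlier glucose value may exist. This stands as a limit. It does not rescue the text, because every pre-operative reading that is described is post-treatment and nothing points to another.

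**A reader might infer that the model must understate liraglutide.** The article does not support a direction. That reading requires lower pre-operative glucose in the liraglutide arm net of all arm rules. Liraglutide patients have mealtime as well as long-acting insulin halved and then all insulin withheld, while bolus patients on long-acting or NPH insulin alone still receive half. In insulin users the net shift could be upward, and the bias would then exaggerate the effect.

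**A reader might infer that the main results are at risk.** They are not. The glucose comparisons at 1 h, 4 h and day 1 use Kruskal-Wallis and Mann–Whitney tests without a baseline covariate, and change in glucose is not among the listed outcome measures.

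**A reader might infer that treatment is absent from the model.** It lacks a main effect, but it appears in the garbled interaction. If categorical treatment by time was meant, arm contrasts are still available.

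**Other inferences the text does not establish.** No SPSS procedure is named, so loss of patients with a missing time point is not shown. Skewed raw glucose does not by itself invalidate an ANOVA with about 95 patients per arm, since the assumption concerns residuals. A raw change score would remove the whole shift, but the plan includes the baseline covariate, and with it change and level give the same arm contrast.

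**Conclusion.** The point holds, at moderate severity. As described, the baseline glucose covariate is a post-randomisation value, so the adjusted contrast does not estimate the total effect of the assigned strategy. The model sentence is also mis-specified.

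The size and sign of the bias cannot be derived from the article. For a true effect of −1.0 mmol/l, assumed slopes of 0.3 to 0.7 and assumed shifts of −1.0 to +0.5 mmol/l give estimates from −0.30 to −1.35. If the assigned treatments happen to leave pre-operative glucose equal across arms, there is no bias. The conclusion assumes that no earlier glucose value serves as baseline. It concerns the supporting change-in-glucose analysis only.

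**What to change.** Replace the model sentence with wording such as:

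> Postoperative glucose (readings to be named) will be analysed in a repeated-measures model with arm, time as a categorical factor, and arm by time, adjusted for the insulin-use stratum and HbA1c. Glucose measured 1 h or 30 min before surgery will not be a covariate; it will be reported by arm as a post-randomisation outcome.

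HbA1c is already collected. Although drawn 1 h before surgery, it is not materially moved by less than a day of treatment. Insulin use is the randomisation stratum. If the full protocol holds a glucose value taken before the first liraglutide dose and the insulin changes, that value may be used instead, provided it is defined as such.

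The outcome should be the postoperative level. Dropping the covariate while keeping change from the pre-operative reading would act like b = 1: with d = −0.5, −1.0 − 1 × (−0.5) = −0.5 mmol/l.

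A log scale and a particular covariance structure are optional and not part of this correction. The cost is protocol or analysis-plan wording; no new data, visits or patients are needed.

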## Discussion

Insulin infusion has been a long established regime for the treatment of DM in the perioperative period and is frequently combined with glucose and potassium for safety reasons [5, 25]. Moreover, a continuous infusion of glucose might reduce peripheral insulin resistance [26]. An alternative for the GIK infusion is an intravenous insulin bolus regime. Although no difference was seen in perioperative glucose control in insulin naïve- and insulin-dependent patients, an intravenous bolus regime might be less time consuming than a GIK infusion plus bolus regime [27, 28]. GLP-1 agonists have potential advantages over established DM treatments with insulin during the intraoperative period, due to the low risk of hypoglycaemia. For proper execution of all regimes, perioperative glucose measurements are mandatory.

Since the start of GLP-1 treatment, it has been suggested that the use of GLP-1 agonists is associated with an increased risk of pancreatitis [29]. However, patients with DM type 2 and obesity, regardless of treatment, have an increased risk of developing pancreatitis compared to patients without DM [30]. A recent meta-analysis of 55 randomized controlled trials (n = 33,350) showed no increased risk for pancreatitis in patients using GLP-1 agonists (OR 1.05, 95% CI 0.37 to 2.94) [31]. Also in a large observational trial with over 20,000 new incretin users, no increased risk for pancreatitis was found when compared to patients with DM using sulfonylureas, HR 1.00, 95% CI 0.59 to 1.70 [32]. Although these studies do not completely exclude the possibility of a slightly elevated risk of pancreatitis when using GLP-1 agonists, they are reassuring and an encouragement for more clinical trials using these new substances.

We think that the combination of perioperative use of GLP-1 agonists compared with more established perioperative treatment regimes, makes this a relevant trial on the optimal intraoperative treatment of DM during non-cardiac surgery.

## Abbreviations

DM: Diabetes mellitus
GIK: Glucose-insulin-potassium
BR: Bolus regime
LG: Liraglutide
GLP-1: Glucagon like peptide-1
ICU: Intensive care unit
CRF: Case report form
NPH: Neutral protamine Hagedorn
OR: Odds ratio
HR: Hazard ratio
CI: Confidence interval.
